## Abstract

**Introduction::**

Cesarean section is a common operation in obstetrics, and the incidence of insufficient breast milk is high in parturients undergoing cesarean section. Studies have shown that acupuncture or massage at related acupoints can promote the secretion and excretion of milk. These external treatments are quick, safe, and effective. On the other hand, they can avoid the potential risk of changes in milk composition that may be caused by the use of drugs. Pestle needle therapy is a new branch of traditional acupuncture, and pestle needle operation does not need to break the skin. The pestle needle has good clinical efficacy and safety in cervical spondylosis, insomnia, fatigue, depression, and so on, but few studies have focused on the effect of pestle acupuncture for patients with lactation insufficiency after cesarean section. This study aims to determine whether pestle needle therapy is effective and safe in the treatment of postpartum milk deficiency.

**Methods::**

This is a 2 parallel-group, assessor-blinded, randomized controlled trial.128 patients with lactation insufficient after cesarean section will be recruited and randomly divided into control group and the pestle needle group in a 1:1 ratio. The control group will receive routine nursing care of milk deficiency. In the pestle needle group, pestle needles will be used to operate on the acupoints such as bilateral Shao ze (S11), bilateral Ru gen (ST18), Dan zhong (DU14), 8 array acupoints of Shen dao (DU11) and so on. It will be operated once a day for 5 days. The primary outcomes are milk yield, degree of breastfilling, degree of milk siltation and other milk deficiency symptom, and serum prolactin. Secondary outcomes include syndrome of traditional Chinese medicine, such as facial expression, fatigue, loss of appetite, and so on.

**Discussion::**

Pestle needle therapy based on acupoint and meridian theory may increase milk secretion and excretion, which will provide a new intervention means to promote breastfeeding and have great significance to guide clinical treatment.

**Trial registration number::**

ChiCTR2000039752.

## Introduction

1

In some parts of China, the rate of cesarean section is as high as 43.82%,^[1]^ and the rate of advanced age puerpera is as high as 50.34%.^[2]^ Between 2008 and 2013, the rate of cesarean section in southeastern Brazil increased from 35.1% to 42.7%.^[3]^ compared with mothers who had spontaneous vaginal delivery, mothers who had cesarean section delivery were lower in the rate of exclusive breastfeeding and had 2.25 times the odds of giving prelacteal feeds.^[4]^ Traditional Chinese medicine (TCM) believes that fasting before cesarean section, loss of blood during operation and poor diet after operation lead to biochemical passivity of milk caused by deficiency of both qi and blood.^[5]^ On the other hand, incision pain, poor sleep, and depression lead to galactostasis by liver qi stagnation. Modern medicine found that the neutrophil-lymphocyte ratio in the blood of mothers who had cesarean section was higher than that of vaginal delivery, and the synthesis of mitochondrial adenosine triphosphate decreased, resulting in delayed lactation or lactation insufficiency.^[6,7]^ Breastfeeding can provide the most suitable nutrients and adequate water for the child, regulate intestinal flora,^[8]^ prevent infection, reduce neonatal mortality,^[9]^ enhance brain development, reduce postpartum hemorrhage, reduce the risk of breast and ovarian cancer, reduce postpartum pain,^[10]^ promote postpartum recovery, and emotional communication between mothers and infants.^[11]^ The lack of breast milk has corresponding harm to both mother and baby.

Pestle acupuncture as a unique branch of traditional acupuncture,^[12]^ its thought of syndrome differentiation is consistent with the theory of TCM, and its characteristic acupoints are Bazheng acupoints (8 array acupoints) and Heche Road (the road for the vehicle).^[13]^ Draw a circle with 1 acupoint as the center and a certain distance as the radius, and then divide the circle into 8 equal parts to form 8 array acupoints in the outer circle. The distance from the center of the circle to the outer 8 array is divided into 3 equal parts, which is drawn into 2 circles that form the inner 8 array and the middle 8 array. The pathway which qi and blood run is called the Heche Road. There are 7 Heche Roads on the back, which one is the posterior median line and the other 6 are parallel lines of 0.5 cun, 1.5 cun, and 3 cun apart from the posterior median line. There are 4 different specifications of pestle needle tools for operation of different acupoints. Kuixingbi is about 8 cm in length, which one end is oval shape and the other end is blunt pestle. Jingganchu is about 10.5 cm in length, which one end is circular arc and the other end is blunt pestle. Wuxingsantaichuis about 11.5 cm in length, which one end is 3 pins in line and the other end is 5pins in blossom shape. Qiyaohunyuanchu is about 10.5 cm in length, which one end is circular arc and the other end is 7 pins stand in parallel. The special acupoints and tools of the pestle needle are shown in Figures 1 and 2.

**Figure 1 F1:**
[figure not shown]
Unique acupoints of pestle acupuncture.

**Figure 2 F2:**
[figure not shown]
Pestle needle tool (from right to left): Kuixingbi, Jingganchu, Wuxingsantaichu, and Qiyaohunyuanchu.

Compared with traditional acupuncture, pestle needle does not pierce into the skin and avoids the pain that may be caused by acupuncture. At present, The pestle needle has good clinical efficacy and safety in the treatment of more than 10 diseases such as cervical spondylosis, insomnia, lumbocrural pain, sub-health, and so on.^[14–17]^ There are more than 200 articles of pestle needle published on China National Knowledge Infrastructure, but there is no English literature involved. This plan aims to introduce this special school of acupuncture and promote the spread of pestle needle. At the same time, it also explores the effective intervention therapy of pestle for postpartum milk deficiency.

## Methods/Design

2

### Study design

2.1

This is a pragmatic, parallel, 2-armed randomized controlled exploratory study. The protocol was reported in accordance with the Standard Protocol Items. The flow chart of the experiment is shown in Figure 3.

**Figure 3 F3:**
[figure not shown]
Trial flow chart.

### Study setting, recruitment and ethics

2.2

This study was approved by the Ethics Committee of the affiliated Hospital of Chengdu University of TCM, and will operate in the Department of Obstetrics of the affiliated Hospital of Chengdu University of TCM. The study plans to recruit 128 patients with lactation insufficiency after cesarean section. The researchers will select qualified subjects according to strict inclusion and exclusion criteria, and patiently inform the subjects of the purpose, method, benefits, and risks of the study. Sign a written informed consent form after obtaining the patient's consent. Patient privacy will be protected and each patient will be assigned a unique random number, which is the unique direct identifier on all case report forms.

### Inclusion criteria

2.3

(1)Diagnosis of lactation insufficiency according to the standards for diagnosis and curative effect of Chinese medical symptom criteria.^[18]^(2)Women diagnosed as lactation insufficiency in 48 hours after delivery.(3)Age 20 to 40 years.(4)Women undergoing cesarean section at 37 to 42 weeks of pregnancy.(5)The Apgar score of baby is 8 to 10.^[19]^(6)The length of hospital stay is not less than 7 days to guarantee the completion of 5 treatments.(7)Willing to breastfeed.(8)Sign the informed consent form and volunteer to participate in this study.

### Exclusion criteria

2.4

(1)Do not exhaust or eat after cesarean section.(2)Abnormal breast development, breast feeding difficulties caused by a history of mastitis, sunken nipples, and chapped nipples.(3)With serious primary diseases or psychosomatic diseases.(4)With gestational diabetes mellitus and gestational hypertension.(5)With postpartum hemorrhage and history of allergy.(6)Have taken drugs for the treatment of postpartum milk deficiency.(7)With skin allergy and intolerance to pestle

### Randomization and blinding

2.5

The randomization sequence will be generated by computer using excel software (Excel 2010 developed by Microsoft; Washington, DC), and using block randomization with a block size of 4 via a central randomization system. Put the random distribution card into opaque envelopes and number the envelopes. The number of the envelopes is the same as that of the random distribution card. When qualified subjects enter the study, open the envelopes in order and carry out treatment according to the grouping. The randomized scheme will be designed by a nursing graduate student in the research group, who will not participate in the clinical implementation phase of the study. Data collectors and statistical analysts will not know the grouping of patients. It is a pity that patients and operators could not be blinded in this study.

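### A single published block size of 4, in a one-department trial with unblinded operators, makes about one allocation in three foreseeable to anyone tracking the sequence, and the route that conceals allocation is unclear

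*Protocol article*

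**What the plan says.** All references are to the protocol article.

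- **Sequence (section 2.5).** "The randomization sequence will be generated by computer using excel software", and in the same sentence "using block randomization with a block size of 4 via a central randomization system". One block size is given; no variation in size is mentioned. The abstract gives the ratio: women are "randomly divided into control group and the pestle needle group in a 1:1 ratio".
- **Release (section 2.5).** "Put the random distribution card into opaque envelopes and number the envelopes". Then: "When qualified subjects enter the study, open the envelopes in order and carry out treatment according to the grouping".
- **Blinding (section 2.5 and abstract).** "It is a pity that patients and operators could not be blinded in this study". Data collectors and analysts are to be kept unaware of group, and the abstract describes the trial as assessor-blinded.
- **Setting (section 2.2).** The trial "will operate in the Department of Obstetrics of the affiliated Hospital of Chengdu University of TCM". The researchers select eligible women. The only person expressly kept out of the clinical phase is the graduate student who designs the scheme (section 2.5).

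**The concern.** Within a permuted block of known size, the last allocations follow from the earlier ones. Three features make this usable here. The block size is fixed and in print. There is one department, so there is one local sequence to follow. Operators see every allocation they treat, and the text does not keep them away from recruitment.

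Foreknowledge matters only if someone can act on it, and there is some room for that. The diagnosis of lactation insufficiency is symptom-based (section 2.3), and some exclusions, such as serious primary or psychosomatic disease (section 2.4), need judgement. A recruiter who expects a particular arm could, knowingly or not, press harder for one woman than for another. The milk deficiency score, one of the two main outcomes, is graded by judgement, so a difference in prognosis at entry would carry into it.

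The route of release decides how much protection there is beyond the block size. Central release after registration prevents opening ahead or out of order. Envelopes held on site rely on staff discipline. The text names both elements without saying what the central system does once the envelopes are in use.

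**Working it through.** **Inputs from the article.** Block size 4, allocation 1:1, N = 128, so 128/4 = 32 blocks. From section 2.12: SD 1.23, difference 0.77, two-sided alpha 0.05, beta 0.1, dropout 20%.

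**The plan's own figure.** The article gives no figure for predictability. Its sample size reproduces: 2 × [(1.96 + 1.28) × 1.23/0.77]² = 53.6 per group, stated as about 53; 53 × 1.2 = 63.6, so 64 per group and 128 in total. With 20% loss, 64 × 0.8 = 51.2, so about 51 per arm are analysed.

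**Certain allocations.** A 1:1 block of 4 has six equally likely orders. An allocation is certain once one arm of the block is used up.

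| Orders | Number | Certain allocations in the block |
|---|---|---|
| AABB, BBAA | 2 | 2 (third and fourth) |
| ABAB, ABBA, BAAB, BABA | 4 | 1 (fourth) |

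Mean = (2×2 + 4×1)/6 = 1.333 per block; 1.333/4 = 33.3%; 32 × 1.333 = 42.7, about 43 of 128 (minimum 32, maximum 64).

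**Best guessing** (always guess the arm with more places left). The chance of being right at positions 1 to 4 is 1/2, 2/3, 2/3 and 1. At position 3 this is 1/3 × 1 + 2/3 × 1/2 = 2/3. The sum is 2.833, and 2.833/4 = 70.8%, against 50% by chance.

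**Illustrative consequence.** Assumption, not in the documents: women enrolled when one arm is foreseen have prognosis shifted by s SD upwards, and when the other arm is foreseen by s SD downwards. If f is the net share of allocations correctly foreseen (right minus wrong), bias = 2 × s × f. Acting on certain allocations only, f = 1/3. Acting on best guesses, f = 2 × 0.7083 − 1 = 0.417. Type I error is the two-sided t-test rejection probability at 51 per arm, with non-centrality bias × √(51/2).

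| s (SD each way) | Acting on | Bias (SD) | Bias in points (× 1.23) | Share of 0.77 | Type I error |
|---|---|---|---|---|---|
| 0.25 | certain only | 0.167 | 0.21 | 27% | about 13% |
| 0.25 | best guesses | 0.208 | 0.26 | 33% | about 18% |
| 0.125 | certain only | 0.083 | 0.10 | 13% | about 7% |
| 0.125 | best guesses | 0.104 | 0.13 | 17% | about 8% |
| 0.10 | certain only | 0.067 | 0.08 | 11% | about 6% |
| 0.10 | best guesses | 0.083 | 0.10 | 13% | about 7% |

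The 0.125 rows are the case in which 0.25 SD is the whole gap between women enrolled on the two foreseen arms.

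**What varying the blocks achieves.** Simulation of 400 trials of 128, in which the guesser knows the possible sizes but not the size of the current block:

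| Scheme | Certain | Best guess right |
|---|---|---|
| Fixed 4 | 33% | 71% |
| Random 4, 6 | about 5% | about 69% |
| Random 4, 6, 8 | about 2.5% | about 68% |

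With 4, 6 and 8, about 3 of 128 allocations are certain (128 × 0.025). At s = 0.25, the bias from acting on certain allocations falls from 0.167 to about 0.01 SD (2 × 0.25 × 0.025). The bias from acting on best guesses falls only from 0.208 to about 0.18 SD (2 × 0.25 × 0.356, where 0.356 = 2 × 0.678 − 1), with type I error about 14%.

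**The case against.** Several points on the other side stand and limit the conclusion.

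- **The one-in-three figure is conditional.** It needs someone who knows the block size, knows where blocks start and has followed every allocation in order. The article does not say that recruiters treat patients or that staff are told the block size. It does not rule out either one, and the block size is in print.
- **The two routes need not conflict.** A reader might infer that a central system and envelopes are incompatible. The text does not support that: the central system belongs to the sentence on generating the sequence, and the envelopes to the sentences on release. Central generation with envelope release is coherent. What stands is that the text leaves the concealing route unclear.
- **The bias figures rest on an unsourced shift.** The 18% figure also depends on acting on guesses, many of them only 2/3 likely to be right, and on steering in both directions. It should not be read as the effect of the certain allocations.
- **Eligibility is fairly tight.** There are limits on age, gestation, Apgar score and length of stay, and the diagnosis must be made within 48 hours of delivery, which limits deferral. Syndrome type guides the added acupoints (section 2.6) and is not an eligibility criterion. Willingness to breastfeed is the woman's own. Some discretion remains in the diagnosis and in the judgement-based exclusions.
- **Assessors are meant to be blinded.** A reader might infer that an assessor who learns one allocation can read off the rest of the block. One known allocation makes each other member of the block the opposite arm with probability 2/3, and only if block membership is known.

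**Conclusion.** The concern holds as a weakness in allocation concealment that is cheap to remove. A fixed, published block of 4, one department, unblinded operators and no stated separation of recruiters from operators together allow a tracker of the sequence to know 33% of allocations (about 43 of 128) and to guess 71% correctly. These figures are exact given block size 4 and 1:1 allocation. That anyone would track the sequence or act on it is not shown.

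The effect on the results can only be illustrated. With shifts of 0.10 to 0.25 SD each way at 51 per arm, type I error runs from about 6% to 13% acting on certain allocations and from about 7% to 18% acting on best guesses. The shift is an assumption, so these are not estimates of what will happen in this trial.

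On the release route, the finding is that the text is unreconciled and should be clarified; it is not a proven contradiction.

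**What to change.** 1. Replace the fixed block of 4 by block sizes that vary at random, for example 4, 6 and 8. Do not disclose them to staff who recruit, treat or assess.
2. State one release route in section 2.5, preferably central release of each allocation after eligibility, consent and baseline assessments are recorded. Keep sealed envelopes at most as a back-up, and say what the central system does.
3. If recruitment has begun, apply the new list from the next patient.

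The cost is a new list from the sequence generator, an amended paragraph, and a possible end-of-trial imbalance of at most 4 (half of an unfinished block of 8). Sample size, outcomes and analysis do not change. The gain from varying the blocks is mainly the loss of certainty (33% to about 2.5%). Because best-guess success falls only to about 68%, varying block sizes alone do not remove the risk from guessing; keeping recruiters unaware of earlier allocations as far as practicable would help with that.

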### Interventions

2.6

According to the literature review and pestle acupuncture therapy,^[20,21]^ the following necessary acupoints are selected:bilateral Shao ze (S11), bilateral Ru gen (ST18), Dan zhong (RN 17), 8 array acupoints of Shen dao (DU11) which is formed with Shen dao (DU11) as the center and 3 cun as the radius., Heche Road of Da zhui (DU14) to Zhi yang (DU9). And then, add other acupoints according to different syndrome types of lactation insufficiency. Bilateral Zu san li (ST36) andbilateral Xue hai (SP10) will be used for type of deficiency of qi and blood. Bilateral Tai chong (LR3) and bilateral Qi men (LA14) will be used for type of liver qi stagnation (Table 1). Treatment will be performed with Taiji pestle needle tool which was designed by Li's pestle needle inheritance studio of Chengdu University of TCM. The needle is a patented product and its patent number is 89213016.4. The operator use pestle tool 1 or pestle tool 2 to knock on and stimulate S11, ST18, RN 17, ST 36, SP 10, LR 3, and LA 14 down to the point that the patient can bear, and then relax gently. Next, use pestle tool 3 to stick on the skin and repeatedly draw an S-shaped or 8-shaped figure in 8 array acupoints of Shen dao. Last, The operator use pestle tool 4 massage along the Heche Road of DU14 to DU9. Each treatment lasts 30 minutes, and the strength of the operation should be a slight flush on the skin. Operators need to receive professional training in the operation of pestle needles in advance.

**Table 1 T1:** Locations for acupuncture.

Acupoint	Location
ST18 (Ru gen)	Below the nipple, at the root of the breast, the fifth intercostal space, 4 cun from the anterior median line
ST 36 (Zu san li)	Three cun directly below ST35, and 1 finger-breadth lateral to the anterior border of the tibia
S 11 (Shao ze)	On the ulnar side of the distal segment of the little finger, and 0.1 cun from the nail angle
LR 3 (Tai chong)	On the dorsal side of the foot and in the depression in front of the junction of the first and second metatarsal bones.
DU 9 (Zhi yang)	On the posterior midline, in the depression under the spinous process of the seventh thoracic vertebra.
DU 11 (Shen dao)	On the posterior midline, in the depression under the spinous process of the fifth thoracic vertebra.
DU 14 (Da zhui)	On the posterior midline, in the depression under the spinous process of the seventh cervical vertebra.
RN 17 (Dan zhong)	On the midpoint of the line between the 2 nipples and the intersection of the fourth intercostal space and the anterior midline
SP 10 (Xue hai)	On the medial thigh, 2 cun above the patella, where the medial thigh muscle processes
LA 14 (Qi men)	Below the nipple, the sixth intercostal space, 4 cun from the anterior median line

### Control group

2.7

Breastfeeding for 8 to 10 times a day to stimulate the continuous secretion of milk. Keep breasts clean and let baby suck 1 breast empty and then suck the other. Pregnant women should eat a balanced diet eat soups in each meal, such as fish soup, chicken soup, pig's foot soup and so on. Encourage patients’ families to communicate more with parturients in order to reduce maternal tension. Maintain pregnant women in a good mood and get enough sleep.

### Pestle needle group

2.8

On the basis of the control group, pestle needles will be used for treatment group. The operation time is 30 minutes once a day for 5 days.

### Primary outcome measurement

2.9

The score of milk deficiency symptom and serum prolactin will be taken as the main outcome indicators. The score of milk deficiency symptom include the evaluation of milk yield, degree of breast filling, degree of milk siltation, the quality of milk, the condition of a baby after breastfeeding (Table 2). The total score was between 0 and 28, and the higher the score was, the more serious the milk deficiency symptom was. Among them, the degree of breast filling and the degree of milk siltation should take the average score according to the situation of both sides of the breast.

**Table 2 T2:** The score of milk deficiency symptom.

	Score			
Item	0	2	4	6
Milk yield	Can fully meet the needs of the baby	Can meet 2/3 of the baby's needs	Can meet 1/3 of the baby's needs	There is almost no milk to feed the baby.
Degree of breast filling	The breasts are full, there is a slight swelling pain, and the milk can flow out without squeezing	The breasts are obviously full, and the milk can flow out with squeezing gently	Breast filling is not obvious, and the milk can flow out with squeezing hard	Breast filling is not obvious, and the milk cannot flow out with squeezing hard
Degree of milk siltation	No milk siltation	Have a feeling of milk distension, and cannot relief after breastfeeding.	The breast has tenderness	Persistent pain caused by milk siltation
The quality of milk	Thick	Clear	No milk	
The condition of a baby after breastfeeding	The baby sleeps quietly between 2 breastfeeding.	The baby sleeps a little quieter between 2 breastfeeding.	The baby cries between 2 breastfeeding.	There is almost no milk to feed the baby.

### Secondary outcome measurements

2.10

The score of TCM symptoms was taken as the secondary outcome indicator, including lusterless complexion, fatigue, loss of appetite, pain in chest and flank, depression, and body fever (Table 3). According to the situation, each TCM symptom is divided into none, mild, moderate, severe, and the corresponding scores are 0, 2, 4, and 6.

**Table 3 T3:** The score of traditional Chinese medicine symptoms.

	Score			
Item	0	2	4	6
Lusterless complexion	No	Mild: a slight pallor in the face.	Moderate: lips are pale, but not reach the level of anemia.	Severe: lips are obviously pale and reach the level of anemia.
Fatigue	No	Mild: feel fatigue after heavy activity.	Modera: feel fatigue after moderate activity.	Severe: feel fatigue after mild activity.
Loss of appetite	No	Mild: find food tasteless, no reduction in food intake.	Moderate: A loss of appetite and a slight reduction in food intake.	Severe: have no appetite and hardly eat.
Pain in chest and flank	No	Mild: happens occasionally and can be relieved by itself.	Moderate: happens frequently and does not affect the work.	Severe: happens Continuous and affect the work.
Depression	No	Mild: depression in a small part of the time.	Moderate: depression in most of the time.	Severe: depression in all the time.
Body fever	No	Mild: The body is slightly hot, without sweating.	Moderate: The body is hot and slightly sweaty.	Severe: The body is hot and sweating continuously.

